### Secondary indicator

Motor symptoms and daily living abilities

UPDRS Ⅱ and Ⅲ: The scale is divided into four parts. The first part evaluates the patient’s mental behaviours and emotions. Part Ⅱ assesses the patient’s ability to live a daily life. Part III assesses the patient’s motor functions. The total score in part IV reflects patient complications. We selected Parts Ⅱ and Ⅲ to evaluate the daily living activities and motor functions of patients, respectively.Revised Hoehn-Yahr Grading Scale: The scale is divided into eight stages, from 0 to 5 (0, 1, 1.5, 2, 2.5, 3, 4 and 5), to evaluate disease severity.

### Adverse events

Adverse events (AEs) occurring during the study are recorded using a Case Report Form. For this trial, an AE will be defined as adverse and unexpected signs, symptoms or diseases associated with the intervention, such as falls, joint injuries, hypertension, etc. Participants will be asked about their medical history and any AEs they have experienced before training begins, and AEs will be recorded after each intervention. The principal investigator will be notified within 24 hours if a serious AE occurs. If subjects withdraw from the trial due to any AE, the study team will follow-up accordingly or until the AE is resolved, This information will be recorded in the original file. The principal investigator manages all safety reports. Any AEs relating to the intervention will be reported to the Ethics Review Committee of the Affiliated Hospital of Shandong University of Chinese Medicine.

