### Methods and analysis

The study is a two-arm, randomised, parallel-controlled trial with assignment-hiding and evaluator blindness. The main objective is to investigate the effects of Zhan Zhuang on upper limb static tremor and aerobic capacity in patients with mild-to-moderate PD, so as to provide a safe, effective, low-cost and easy-to-master aerobic exercise therapy for patients with PD.

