### Statistical analysis

We will evaluate the outcome and collect data at week 9 of the intervention and follow-up at week 17 of the intervention (table 1). Basic patient information, mobile phone exercise test data, CRST scores and UPDRS (Ⅱ and Ⅲ) scores will be exported to our computer system CSV format.

**Table 1 T1:** Data collection schedule and visit assessments

Measures	Baseline week	Intervention period (0–8 weeks)	End of intervention (9 weeks)	Follow-up period (9–16 weeks)	Follow-up (17 weeks)
Participant characteristics	**√**				
Mobile phone tremor test	**√**		**√**		**√**
CRST (A+B)	**√**		**√**		**√**
CPET	**√**		**√**		**√**
UPDRS (II, III)	**√**		**√**		**√**
Hoehn-YaHr	**√**		**√**		**√**
Adverse events^*^		**√**		**√**	
Combined medication^†^		**√**		**√**	

*Adverse events: Adverse event at any visit during treatment sessions and over the 36 weeks will be monitored. The research team will review all trial protocols, monitor patient safety and investigate any adverse events.

†Combined medication: Patients will be asked if they have used other medications during the treatment. If they have, medications type and dose will be recorded.

CPET, cardiopulmonary exercise test; CRST, Clinical Tremor Rating Scale; UPDRS, Unified Parkinson’s Disease Rating Scale.

SPSS V.17.0 statistical software will be used for data processing and analysis: (1) Measurement data will be processed using the mean SD (x^2^ ±s); (2) T-tests will be used to assess: normal distribution and homogeneity of the overall variance in both samples; (3) T-tests will be used to assess: normal distributions, but uneven overall variance; (4) The Wilcoxon rank-sum test will assess if date does not conform to a normal distribution; p value<0.05 indicates statistical significance.

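### The adverse event definition is narrow and conflicts with the rest of its own section, and the 36-week monitoring footnote does not fit a schedule that ends at week 17

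*Protocol article*

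**What the plan says.** Four statements in the Adverse events section bear on what gets recorded:

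- Scope: "Adverse events (AEs) occurring during the study are recorded using a Case Report Form".
- Definition: "an AE will be defined as adverse and unexpected signs, symptoms or diseases associated with the intervention", followed directly by examples, "such as falls, joint injuries, hypertension, etc".
- Timing: participants are asked about earlier AEs before training starts, and then "AEs will be recorded after each intervention".
- Onward reporting: "Any AEs relating to the intervention will be reported to the Ethics Review Committee".

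The Statistical analysis section gives the calendar: "We will evaluate the outcome and collect data at week 9 of the intervention and follow-up at week 17 of the intervention". Table 1 has columns for baseline, weeks 0–8, week 9, weeks 9–16 and week 17. The AE row is ticked under weeks 0–8 and weeks 9–16 only. The footnote to that row says: "Adverse event at any visit during treatment sessions and over the 36 weeks will be monitored".

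The Methods and analysis section states the purpose of the trial in terms that include safety: "so as to provide a safe, effective, low-cost and easy-to-master aerobic exercise therapy".

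**The concern.** A definition that requires an event to be unexpected and related applies two judgements before anything is written down. An expected effect of exercise, or an event put down to the underlying disease, would not qualify. Relatedness and expectedness are normally recorded about an event after it has been captured. If they decide capture, the discarded events are gone, and no later analysis plan can recover them.

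The loss could also differ between arms. Both arms exercise five times a week for 30 minutes, but Study design and setting gives the name intervention group to the Zhan Zhuang arm and control group to the walking arm. A fall while walking might then not count as related to the intervention, while a fall during Zhan Zhuang would.

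The timing raises a second, separate problem. Staff cannot tell from Table 1 and its footnote when monitoring stops, or whether AEs are to be sought at the assessment visits. A trial that means to offer a safe therapy, with 36 patients per arm, will see few events, so a handful missed could change the safety picture.

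**Working it through.** **1. The definition against the rest of its section.**

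| Statement in the Adverse events section | What it implies about scope |
|---|---|
| Definition: unexpected and associated with the intervention | Expected or unrelated events are not AEs |
| Opening sentence: AEs arising during the study go on the Case Report Form | Gives no limit of its own by cause or expectedness |
| Examples: falls, joint injuries, hypertension | Foreseeable events are AEs |
| Ethics committee receives AEs related to the intervention | Unrelated AEs also exist; otherwise the qualifier does nothing |

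The last two rows do not fit the definition, and the opening sentence reads more widely than it does. Staff could reasonably follow either a narrow or a wide rule.

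**2. The meaning of intervention.** Study design and setting uses intervention group for Zhan Zhuang only. Table 1 uses intervention period for both arms. Whether an event caused by walking meets the definition depends on which usage applies, and the article does not say.

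**3. The monitoring period.** Inputs: 36 weeks (Table 1 footnote); last visit at week 17 and last AE tick covering weeks 9–16 (Table 1); intervention of 8 weeks (Abstract).

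- Beyond the last visit: 36 − 17 = 19 weeks, and 19/36 = 53% of the stated period.
- Beyond the last ticked AE period: 36 − 16 = 20 weeks.
- Attempts to reproduce 36 from the article's own periods: 8 + 8 = 16; 8 + 17 = 25; 9 + 17 = 26; 16 + 17 = 33; 2 × 17 = 34. None gives 36.

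**4. The visits.** The footnote covers any visit. Table 1 places the cardiopulmonary exercise test at baseline, week 9 and week 17, and the AE row is blank at all three. That test is a symptom-limited maximal treadmill test. An event during it falls outside the ticks, and may fall outside a definition tied to the intervention. Conversely, AEs are ticked for weeks 9–16, but recording after each session offers no occasion there, because Table 1 shows those weeks as follow-up after the intervention has ended.

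**5. Size.** The article gives no AE rate and no basis for the share of events that the definition would capture. As an illustration on assumed values only, the expected number of patients counted in an arm is 36 × risk × share captured:

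| Share captured (assumed) | Risk 10% (assumed) | Risk 30% (assumed) |
|---|---|---|
| 100% | 3.6 | 10.8 |
| 75% | 2.7 | 8.1 |
| 50% | 1.8 | 5.4 |
| 25% | 0.9 | 2.7 |

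The direction follows from applying the definition literally. The size does not follow from the document.

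**The case against.** The strongest reply is that this is loose drafting. Falls and joint injuries are named as AEs, so the harms one would most expect from standing or walking exercise would probably be captured. The opening sentence can be read as covering whatever arises in the study, and the ethics-reporting sentence presumes a wider set. This stands as far as it goes: under-counting is a risk of the literal definition, not a certainty.

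A reader might infer three stronger things that the article does not support.

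- **That a safety comparison between arms cannot be carried out.** The article writes no such comparison, and its absence is no finding, because an analysis plan may hold it. AEs can still be tabulated by arm to week 16 or 17. Only the 36-week window cannot be met on the schedule shown.
- **That unblinded staff decide which events count.** Training personnel and patients are unblinded, but the article does not say who judges relatedness or expectedness. It says that the principal investigator manages safety reports, without giving that person's blinding status; testers and data collectors are blinded.
- **That events are sought less carefully in the walking arm.** A Qigong master, a safety assistant and an exercise calendar are described for Zhan Zhuang and not for walking. This is silence in a condensed article, and the AE row of Table 1 does not distinguish the arms.

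It is also fair to say that the 19-week gap shows a discrepancy in one footnote. It shows no bias in the counts for weeks 0–16.

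**Conclusion.** The point holds in two separate parts.

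First, the AE definition is narrower than the section around it and inconsistent with it. If applied as written, it risks under-counting expected or judged-unrelated events. The risk may be unequal by arm if intervention is read as Zhan Zhuang only. Both statements rest on a literal reading, and the size of the effect cannot be estimated.

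Second, the monitoring period is contradictory on its face: 36 weeks against a last visit at week 17, a difference of 19 weeks, and any visit against three visits with no AE tick. This part needs no assumption.

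Neither part touches the primary outcomes. The definition is still worth correcting before recruitment, because events that are not recorded cannot be recovered at the analysis stage.

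**What to change.** - Define an AE as any untoward medical occurrence after randomisation in either arm, regardless of expectedness or suspected cause.
- Record relatedness and expectedness as separate fields on the Case Report Form. State whether relatedness refers to the assigned exercise in either arm and whether it includes the study tests.
- Apply the same recording to both arms, including during weeks 9–16 when there are no sessions.
- Reconcile the 36-week footnote and the AE ticks with the 17-week schedule: either correct the figure or add the contact that it implies, and make the row agree with the footnote on visits. If baseline testing precedes randomisation, say how events at that test are recorded.

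The cost is a change of wording in the definition, the form and the footnote, and more minor events to record in both arms.

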### Study design and setting

The study will be conducted in the Affiliated Hospital of Shandong University of Traditional Chinese Medicine. We will include 72 patients with PD with obvious upper limb static tremor. Recruitment will begin on 1 June 2022 and run until 1 June 2023. Using the random number table method, 72 patients will be randomly divided into an intervention and control group in a 1:1 ratio. Basic patient information, including gender, age, disease course, education level, residence status and drug-use will be collected. Tremor and motor function tests will be performed at least 8 hours after patients stop taking medication.

The control group will be treated with conventional medicine and routine aerobics. According to the Chinese Guidelines for the Treatment of PD (fourth edition), walking will be selected as the aerobic exercise mode in this group,^27^ five times a week at 30 min each time for 8 weeks. A combined cardiopulmonary exercise test (CPET) (treadmill test) will be used to measure peak oxygen uptake (peakVO_2_) in patients with PD at baseline and after intervention, and also anaerobic threshold (AT) and maximum heart rate (HRmax). During training, patients exercise intensity will be controlled at moderate exercise intensity (HRmax (60%–80%) measured by CPET or 11–13 Rating of Perceived Exertion (RPE). Changes in peakVO_2_ and AT at baseline and after intervention will be evaluated for improvements in aerobic exercise capacity. Walking will be performed about 1 hour after patients take their medication, and the tremor symptoms were resolved or disappeared.

The intervention group will take conventional medicine combined with Zhan Zhuang Qigong. An experienced Qigong master will guide Zhan Zhuang exercise. Week 1 will comprise the learning phase, while weeks 2–8 will be the practice phases, to be performed five times a week at 30 min each time. Intensity HRmax (60%–80%) will be measured using a cardiopulmonary combined exercise test or RPE test grade 11–13. Patients will be issued a training instruction manual and a personal exercise calendar to record the number of weekly exercises and time of each exercise. Zhan Zhuang training will be about 1 hour after patients take their medication, and tremor symptoms were relieved or disappeared. One auxiliary staff member will oversee safety measures.

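### The adverse-event definition admits only unexpected, intervention-associated events, which conflicts with the rest of the protocol, omits test-related harms on its literal wording and leaves the walking arm unclear

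*Protocol article*

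**What the plan says.** The trial-specific definition is in the Adverse events section: "an AE will be defined as adverse and unexpected signs, symptoms or diseases associated with the intervention", with falls, joint injuries and hypertension as examples. The same section also says "Adverse events (AEs) occurring during the study are recorded using a Case Report Form", that "AEs will be recorded after each intervention", and that "Any AEs relating to the intervention will be reported to the Ethics Review Committee". Serious AEs go to the principal investigator within 24 hours.

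Table 1 (Statistical analysis) ticks the AE row for the intervention period and the follow-up period only. The baseline, week 9 and week 17 columns, where the tests are scheduled, are blank in that row. The table footnote reads "Adverse event at any visit during treatment sessions and over the 36 weeks will be monitored" and adds that the team will look into every AE. Neither the row nor the footnote is limited to one arm.

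The objective (Methods and analysis) is framed "so as to provide a safe, effective, low-cost and easy-to-master aerobic exercise therapy for patients with PD". Both arms exercise: "The control group will be treated with conventional medicine and routine aerobics", with walking as the chosen mode.

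**The concern.** Expectedness and relatedness are normally judged for each event after it has been recorded. Here both are conditions of being an AE. An event judged foreseeable, or judged unconnected with the intervention, is then not an AE and need not reach the case report form.

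Two things are at stake. First, the AE count in each arm depends on judgements made before recording, in a trial where participants and trainers know the allocation. A low count could reflect the definition and not safety. Second, serious-event notification and ethics reporting both operate on AEs. On the literal text, an event filtered out by the definition may miss both routes. Events that were never recorded cannot be recovered at analysis.

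**Working it through.** The protocol gives no AE rate, so there is no figure to reproduce. The check sets the passages side by side and then counts the exposure affected.

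**1. Definition against its own examples.** The definition requires the event to be unexpected. Its examples are falls, joint injuries and hypertension. In people aged 50–70 with Parkinson's disease (Inclusion criteria) doing standing or walking training, these are foreseeable. The qualifier and the examples cannot both be applied strictly.

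**2. Definition against the ethics-reporting sentence.** Only AEs related to the intervention go to the ethics committee. That subset has meaning only if unrelated AEs exist, and the definition rules them out.

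**3. Definition against the broader wording.** The opening sentence of the section covers AEs during the study, and the Table 1 footnote promises to look into all of them. Neither carries the two conditions. Staff cannot follow both the narrow and the broad text.

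**4. Test-related harms.** CPET is a symptom-limited maximal treadmill test (Primary outcome), scheduled at baseline, week 9 and week 17 (Table 1). Tremor and motor tests are done at least 8 hours off medication (Study design and setting). Harm from these procedures is not associated with the intervention on a plain reading, and a baseline event precedes it altogether. The blank AE cells in the three assessment columns point the same way.

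- Participants: 72. Assessment points each: 3. 72 × 3 = 216 participant assessments.
- If the protocol's 15% loss all occurs before week 9: 72 × 0.85 ≈ 61 remain, so 72 + 2 × 61 = 194.

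**5. Walking arm.** The section on blinding ties the word intervention to Qigong, and the intervention group is the Zhan Zhuang arm. However, the control-arm paragraph also uses the word for its own before-and-after comparison, and Table 1 has one intervention period for everyone. The word is ambiguous, so the rule for the walking arm is not settled.

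- Walking sessions planned: 5 per week × 8 weeks × 36 participants = 1,440.
- With 15% lost from the start: 1,440 × 0.85 = 1,224.

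**6. Monitoring period.** The footnote gives 36 weeks; the schedule ends at week 17, a gap of 36 − 17 = 19 weeks. This is a separate mismatch in the same AE text and needs settling in the same edit.

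**The case against.** The best defence is that *unexpected* is loose wording for unwanted or unplanned. Falls are named as an example, AEs during the study go on the case report form, the footnote refers to any visit, and participants are asked about AEs before training begins. Read generously, everything is captured. The follow-up column also starts at week 9, so the week 9 test is arguably within a ticked period. Details of case report form fields and AE tables are properly left to the full protocol.

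Part of this stands. It shows that the protocol is inconsistent, not that exclusion is settled, and missing form fields are not the complaint. But the definition is explicit and trial-specific, and condensing the article does not explain its two conditions. The generous reading works only by setting those conditions aside.

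Four stronger inferences are tempting and not supported:

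- *Walking-arm harms are excluded.* No text says so; this is one reading of an ambiguous word, and the AE row and footnote cover both arms.
- *Falls would go uncounted as expected in this disease.* The definition names falls.
- *Unblinded trainers decide what is recorded.* The protocol does not say who records or attributes AEs. Training personnel are unblinded, but data collectors are stated to be blinded. Recording by trainers after sessions is plausible, not stated.
- *Safety cannot be judged at all.* Named harms are to be captured, serious AEs are notified, and withdrawals due to an AE are followed up.

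**Conclusion.** The point holds as a conflict within the protocol that can lose events. The definition is narrower than the text around it and at odds with its own examples. Harms of the tests are the best-supported gap, since the literal definition and the blank cells in Table 1 agree; only the general phrases about the study and any visit point the other way. For the walking arm the defect is uncertainty about the rule, not a stated exclusion. The supportable conclusion is that safety cannot be compared between arms without risk of bias.

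The exposure affected is up to 216 participant assessments (about 194 with early loss of 15%) and 1,440 planned walking sessions (1,224 with the same loss). These count opportunities for an event and assume attendance as planned; they are not estimates of events lost. The efficacy outcomes are unaffected, and safety is listed as neither a primary nor a secondary outcome. This should be fixed, but it does not threaten the main efficacy analysis.

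**What to change.** Replace the definition with one along these lines: an AE is any untoward medical occurrence from enrolment onward, in either arm, including during assessments, whether or not expected and whether or not related to a trial activity. Counting from enrolment, not randomisation, brings the baseline CPET within scope.

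Then:

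- record seriousness, expectedness and relatedness (to Zhan Zhuang, walking, test procedures or other) as separate fields for each event;
- collect AEs in the same way in both arms;
- report all AEs and related AEs by arm;
- reconcile the Adverse events section with Table 1: mark the AE row at baseline, week 9 and week 17, and settle the footnote's 36 weeks against the 17-week schedule.

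The stated recruitment start (1 June 2022) precedes the article's publication (11 July 2022). If participants are already enrolled, the amendment should say how their earlier events will be checked.

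The cost is one definition sentence, a few form fields and an edit to Table 1. More events will be recorded, and the AE table will look less favourable.

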### Statistical analysis

We will evaluate the outcome and collect data at week 9 of the intervention and follow-up at week 17 of the intervention (table 1). Basic patient information, mobile phone exercise test data, CRST scores and UPDRS (Ⅱ and Ⅲ) scores will be exported to our computer system CSV format.

**Table 1 T1:** Data collection schedule and visit assessments

Measures	Baseline week	Intervention period (0–8 weeks)	End of intervention (9 weeks)	Follow-up period (9–16 weeks)	Follow-up (17 weeks)
Participant characteristics	**√**				
Mobile phone tremor test	**√**		**√**		**√**
CRST (A+B)	**√**		**√**		**√**
CPET	**√**		**√**		**√**
UPDRS (II, III)	**√**		**√**		**√**
Hoehn-YaHr	**√**		**√**		**√**
Adverse events^*^		**√**		**√**	
Combined medication^†^		**√**		**√**	

*Adverse events: Adverse event at any visit during treatment sessions and over the 36 weeks will be monitored. The research team will review all trial protocols, monitor patient safety and investigate any adverse events.

†Combined medication: Patients will be asked if they have used other medications during the treatment. If they have, medications type and dose will be recorded.

CPET, cardiopulmonary exercise test; CRST, Clinical Tremor Rating Scale; UPDRS, Unified Parkinson’s Disease Rating Scale.

SPSS V.17.0 statistical software will be used for data processing and analysis: (1) Measurement data will be processed using the mean SD (x^2^ ±s); (2) T-tests will be used to assess: normal distribution and homogeneity of the overall variance in both samples; (3) T-tests will be used to assess: normal distributions, but uneven overall variance; (4) The Wilcoxon rank-sum test will assess if date does not conform to a normal distribution; p value<0.05 indicates statistical significance.

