### Sample size

This study is designed as a randomised controlled trial. The main outcome is the mean relief of upper limb static tremor after treatment. A review of previous studies showed that aerobic exercise could reduce upper limb static tremor amplitude by approximately 60%. It is estimated that the average tremor amplitude of the control group is approximately 76±136 mm, and the intervention group is expected to be reduced by 50 mm after training. The test level α is set at 0.05 (bilateral), the degree of certainty 1-β is set at 0.80 and the control:intervention group ratio=1:1. A sample size of 63 was calculated using *http://powerandsamplesize.com*. However, considering an abscission rate of about 15%, 72 patients with PD will be included.

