## Assessment result

### Primary outcome

(1)Static tremor of the upper limbs

① Mobile phone movement exercise test

Phyphox APP^28^ is based on the Android system (V.1. 1. 9). It collects the static tremor date of the upper limb of patients with an obvious tremor, at a frequency of 100 Hz over 30 s.

Data collection on the static tremor: The patient relaxes, sits in a chair, places his/her hands on the armrest and holds the mobile phone with the screen up on the shaking side. At the same time, patients perform numerical subtraction calculations to distract their attention. The time from the beginning of the tremor is recorded over 30 s.

② The Clinical Tremor Rating Scale (CRST) A+B, CRST-A is used to evaluate the tremor at rest, postural and intentional; CRST-B assesses handwriting (dominant hand only), wide and narrow spiral drawing, straight lines and casting. For the dominant hand, the maximum subscore of hand tremor is 32 for CRST (A+B) and 28 for the non-dominant hand. The higher the score, the more severe the tremor.

(2)Aerobic capacity

Combined Cardiopulmonary Exercise Test (CPET)

The cardiovit CS-200 cardiopulmonary combined exercise test system (SCHILLER, Switzerland) is used for CPET. The treadmill test is performed, and the increasing rate set at 10 W/min. Based on standards from Harbor-UCLA Center Cardiopulmonary Exercise Laboratory, USA, the resting state lung function examination, including fast lung capacity, slow lung capacity, maximum minute ventilation capacity and diffusion function, should be completed first. Symptom limiting maximum CPET is then completed using continuous ramping regimen.^29–31^ CPET is divided into four stages, including 3 min of rest, 3 min warm-up (no treadmill power), then exercise at an increasing power rate of 10 W/min until symptom limiting maximum exercise, followed by more than 5 min of recovery.^32^ Continuous 12-lead ECG, non-invasive cuff blood pressure and oxygen saturation measurements are required during the CPET process. PeakVO_2_, AT, and HRmax are measured and recorded.

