#### Mobile exercise test data

The original form is the acceleration a (m/s) of three axes (X, Y and Z) vector direction, respectively, rotation radian w (rad/s). The MATLAB (version R 2018a, MathWorks, USA) computer program will be used to perform Fourier transformation of the data, and acceleration and rotation radian measurements by smartphone will be converted to corresponding frequency, peak amplitude and speed date. Final phone test data will be presented as the amplitude and frequency of static tremors. Then, normal distribution tests will be conducted. Since the sample size is small (N<5000), the Shapiro-Wilk normal test will be used. P value>0.05 indicates a normal distribution, while p value<0.05 indicates a non-normal distribution.

According to normal distribution test date, if mobile phone exercise test data are normally distributed and the variance uniform, mobile phone exercise test data in patients with PD in different groups will be tested using with two sample independent t-tests. P value<0.05 will indicate if the exercise is statistically significant between groups. If the data are not normally distributed, non-parametric tests (median and Mann-Whitney U tests) will be performed for comparison. P value<0.05 in median tests will indicate if differences in central tendency scores between groups are statistically significant.

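### The protocol lists several primary measures, each judged at p<0.05, but sets alpha and sample size for one main outcome; if any can count as success, the false-positive risk at week 9 is about 11–23%, not 5%.

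*Protocol article*

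**What the plan says.** All references are to the protocol article.

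- **Primary outcome** has two headed items. Static tremor of the upper limbs is measured by the phone test and by CRST A+B. Aerobic capacity is measured by CPET, for which peakVO2, AT "and HRmax are measured and recorded". The secondary list (UPDRS II and III, Hoehn-Yahr) starts only after these.
- **Mobile exercise test data** gives the phone test two readouts: "Final phone test data will be presented as the amplitude and frequency of static tremors". It then states: "P value<0.05 will indicate if the exercise is statistically significant between groups".
- **Study design and setting** judges improvement in aerobic capacity on peakVO2 and AT.
- **Statistical analysis** schedules "data at week 9 of the intervention and follow-up at week 17 of the intervention", and Table 1 ticks the phone test, CRST and CPET at both visits. The general rule is "p value<0.05 indicates statistical significance".
- **Sample size** speaks of one outcome: "The main outcome is the mean relief of upper limb static tremor after treatment". The error rates are "The test level α is set at 0.05 (bilateral") and "the degree of certainty 1-β is set at 0.80". The calculation uses tremor amplitude only.

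**The concern.** An alpha of 0.05 for one main outcome limits the chance of a false positive primary claim to 5% only if one test decides the claim. Here the Primary outcome section gives three instruments the same standing, with five readouts that the plan uses to judge benefit. The analysis text applies the single-test threshold to each. Nothing in the document orders them, splits the alpha or requires all to succeed.

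A significant CRST, tremor frequency, peakVO2 or AT result could therefore be reported as a positive primary finding even if tremor amplitude, the only variable behind the sample size, showed no difference. The trial has 72 patients, so one favourable result among several should not be mistaken for the planned test.

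**Working it through.** **The plan's own figure.** One two-sided test at 0.05 has a false positive risk of 5%. This is the only error rate the plan states, and it matches a single main outcome.

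**Inputs**
- Per-test threshold: 0.05 (Statistical analysis; Mobile exercise test data).
- Instruments under Primary outcome: 3 (phone test, CRST A+B, CPET).
- Readouts used to judge benefit: 5 (amplitude, frequency, CRST A+B, peakVO2, AT). HRmax is left out because Study design and setting uses it to set exercise intensity and does not name it among the variables that show improvement.
- Visits after baseline: 2 (weeks 9 and 17, Table 1).
- Correlation between tests: not given. Assumed common value r, from 0 to 0.7.

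**Formula.** With k independent tests, P(at least one false positive) = 1 − 0.95^k.
- k = 3: 1 − 0.857 = 14.3%
- k = 5: 1 − 0.774 = 22.6%
- k = 6: 1 − 0.735 = 26.5%
- k = 10: 1 − 0.599 = 40.1%

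For correlated tests I took equicorrelated normal test statistics and computed the probability that at least one exceeds 1.96 in absolute value.

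| Tests counted | k | r = 0 | r = 0.5 | r = 0.7 |
|---|---|---|---|---|
| 3 instruments, week 9 | 3 | 14.3% | 12.5% | 10.9% |
| 5 readouts, week 9 | 5 | 22.6% | 18.3% | 14.8% |
| 3 instruments, weeks 9 and 17 | 6 | 26.5% | 20.7% | 16.4% |
| 5 readouts, weeks 9 and 17 | 10 | 40.1% | 28.7% | 21.3% |

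Relative to 5%, week 9 alone gives 10.9/5 = 2.2 to 22.6/5 = 4.5 times. Both visits give 16.4/5 = 3.3 to 40.1/5 = 8.0 times.

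**Sensitivity.** With r = 0.9 between all tests, the risk is 8.4% for k = 3, 10.2% for k = 5, 10.8% for k = 6 and 12.8% for k = 10. A correlation that high between a tremor scale and oxygen uptake is hard to credit, and the risk still exceeds 5%.

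**Cost of the possible remedies**
- Fixed sequence (amplitude, then peakVO2 only if amplitude is significant): if neither has an effect, a false claim needs the first test to reject, so the risk stays at 5%.
- Holm on the two: the smaller p-value is compared with 0.025. For the same 80% power at that level the sample size rises by (2.241 + 0.842)² / (1.960 + 0.842)² = 1.21, about 21%.
- Power of the first step: with the Sample size inputs (difference 50 mm, SD 136 mm) and 36 per arm, 50 / (136 × √(2/36)) = 1.56, and Φ(1.56 − 1.96) is about 34%. This ignores dropout. It is well below the stated 0.80, a separate matter that does not affect the error rates above.

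**The case against.** **Week 17 may not be a primary visit.** The main outcome is set after treatment, aerobic change is judged after the intervention, Table 1 labels week 9 as the end of intervention, and the abstract treats long-term effects as a separate question. This largely stands. A reader might infer that there is no primary time point and double every count. The text does not support that as the main reading, so the week 9 figures lead and the two-visit figures are an upper reading.

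**HRmax.** A reader might count it as a sixth primary readout and reach twelve tests and 46%. It is recorded under Primary outcome, but its stated use is to set training intensity. It should not be counted.

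**Open label.** A reader might add that an open-label trial makes selective reporting easier. Participants and trainers are unblinded, but testers, data collectors and analysts are blinded, and the groups are identified only after the statistics are complete. The multiplicity point stands without that claim.

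**The two sections overlap.** Upper limb static tremor is the first item of the primary list, and trials are often sized on one of several primaries. True: the conflict is over number and priority, not over incompatible outcomes.

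**An unseen analysis plan may handle multiplicity.** An adjustment method could properly sit there, and its absence here is no finding. But the protocol itself fixes several primaries, a 0.05 rule for each and a single main outcome. An analysis plan would have to override one of these.

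**Extra tests on the phone data.** For non-normal data both a median test and a Mann-Whitney test are named. The median test appears to be the one read for central tendency, so the second is not counted.

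**Conclusion.** The point holds. The Primary outcome and Sample size sections conflict, and the p<0.05 rule applied to every comparison does not keep the stated 5% for the primary claim. At week 9 the risk of at least one false positive is about 11–14% for three instruments and 15–23% for five readouts. It reaches 16–27% (six tests) or 21–40% (ten tests) only if week 17 also counts.

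These figures rest on two assumptions: that any one significant primary would count as success, which nothing in the document rules out, and that the tests share a common correlation between 0 and 0.7. If all primaries had to be significant, there would be no inflation, but no such rule is stated.

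**What to change.** Before any outcome data are seen, make the Sample size and Primary outcome sections agree:

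1. Name one primary endpoint: phone-measured static tremor amplitude at week 9 (end of intervention), the variable already used for the sample size, tested at two-sided 0.05.
2. Move tremor frequency, CRST A+B, AT and all week 17 results to secondary, reported with confidence intervals. Say that HRmax is recorded but is not an efficacy endpoint.
3. If aerobic capacity is to stay confirmatory, test peakVO2 at week 9 second, at 0.05, only if amplitude is significant. Otherwise make it secondary too.

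This takes about one paragraph in the protocol and a matching registry update. Data collection does not change. The price is that fewer outcomes can be called confirmatory, and that peakVO2 is formally tested only after a significant amplitude result, which on the plan's own inputs has about 34% power. Holm on the two endpoints would avoid that dependence, but it is not free: its first step at 0.025 needs about 21% more patients for the same power.
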